### Outcome measures

#### Primary outcome

The primary outcome is change in adjusted BMI z-score at the end of the active intervention period, 6 months post-enrollment. Adjusted BMI z-scores account for child age and gender and allow the evaluation of changes in BMI z-scores within the upper range of z-scores expected during this trial [28]. Adjusted BMI z-score is assessed in all three arms. The primary comparison is between the two active intervention groups at 6 months. The 12-month time point serves as an evaluation of maintenance of any changes post-intervention (Fig. 3).

**Fig. 3 Fig3:**
[figure not shown]
SPIRIT (Standard Protocol Items: Recommendations for Interventional Trials) figure: Primary and secondary outcomes, covariates, and assessment time points for parent–child dyads in the trial

We obtain the height and weight measurements for each enrolled child after removal of shoes and any outer garments (e.g., coat), allowing one layer of clothing to remain. Height measurements are obtained by using a stadiometer (model 233, Seca, Hamburg, Germany) and weight measurements with a portable, flat scale (model 869, Seca). Height and weight measurements are obtained in duplicate, and a third measurement is obtained if the two initial values differ by more than 1 cm for height or 0.5 kg for weight. The mean of the two closest measurements is used for BMI calculations, with the mean of all three values used if the measurements are equally-spaced.

#### Secondary outcomes

Blood pressure, waist circumference, self-efficacy, feeding practices, dietary intake, physical activity, sleep, and screen time are assessed by interviewer-administered survey at baseline, at end of the 6-month intervention period, and at the 12-month time point in all three intervention arms. The home food environment assessment is completed only in intervention and active control dyads at baseline and 4-month follow-up.

Blood pressure and waist circumference: Trained research personnel obtain blood pressure readings on child participants by using a standardized sphygmomanometer (model CONTEC08A, Contec Medical Systems, Qinhuangdao, China) on both arms in duplicate for each arm, as tolerated, and the mean of both values for each arm is used. Waist circumference is obtained by using the anterior superior iliac crest and umbilicus as anatomic landmarks, in triplicate with the mean of two measurements within 1 cm recorded or the mean of all three values if equally spaced.

Self-efficacy: The Generalized Self-Efficacy Scale (GSES) (12 items) [29, 30] is administered as well as parental self-efficacy questions related specifically to diet and physical activity practices and behaviors [31]. The GSES ranges from a score of 12 to 60 (higher scores indicate greater self-efficacy), and domains of initiative, persistence and effort are examined as subscales. The GSES has good internal consistency; Cronbach’s alpha values are 0.86 for the overall scale and 0.77–0.83 for the subscales [30]. The parental self-efficacy questions had been developed and tested previously among parents of preschool children, and the overall scale had a Cronbach’s alpha of 0.94 [31]. We added two questions on self-efficacy related to consistency in rules around snacking and communication with other providers; although we collected feedback from representative parents on these questions, these two queries have not otherwise been validated.

Comprehensive Feeding Practices Questionnaire (CFPQ) subscales: The intervention targets the food environment and potentially influences parental monitoring and control. Thus, we administer three subscales of the CFPQ to parents (environment, monitoring, and control subscales) [32]. The CFPQ is composed of a five-point, Likert-like scale ranging from “never” to “always” on responses related to practices and has a continuous outcome.

Dietary intake: The Block Kids Food Screener (BKFS), developed by NutritionQuest (Berkeley, CA, USA), is administered to parents to assess their child’s dietary intake. The BKFS is an abbreviated version of a food frequency questionnaire that queries 41-food items and can be used to compare consumption and patterns between groups [33].

Physical activity, screen time, and sleep: Outdoor physical activity is queried in a structured series of seven questions asking about days of the week spent engaged in outside play and then asking about specific times of the day with the reference period being the previous week [34]. Screen time is assessed by using questions from the National Survey of Early Childhood Health [35]. Sleep duration is assessed with questions about usual bedtime and wake times by using the method from the Zurich Longitudinal Studies to establish reference ranges for sleep duration in children [36]. These questions do not assess sleep latency or awakenings per se.

Home food environment: The home food and physical activity environment is assessed in the two parent mentor arms (positive deviance and active control) by using a standardized assessment tool adapted from a prior study [37]. This is a parent-reported observation tool that has been evaluated by comparing assessments of the home food and physical activity environment between observers, and only items with a kappa statistic of more than 0.61 are retained. Parent mentors administer the paper survey with parents in their homes and return it to the research office in a stamped envelope.

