#### Parent mentor recruitment and training

Potential parent mentors are identified within each early childhood care center by the Head Start staff as parents who have taken on an active or leadership role within the center. They are then recruited to participate on the basis of interest and availability. All parent mentors have a child attending the center and are required to have conversational-level English and Spanish proficiency. Parent mentors are assigned parent mentees after randomization with the expectation that parents mentor up to 14 parents per month.

All parent mentors undergo two-day training by the research staff. The first day of training covers general mentoring skills, such as active listening and supportive feedback, as well as confidentiality and the logistics of the program. The second day of training is specific to the curriculum they are going to use: either the positive deviance curriculum or the *We Can!* curriculum; each curriculum is described in detail in the following section. In regard to the positive deviance arm, the parent mentors themselves are not positive deviants per se; rather, they receive training in how to mentor other parents on the strategies used by positive deviants. Each potential mentor practices presenting portions of the curriculum. Parents participating in the mentor training are compensated for their time. Research staff observe parents during the training, and the final parent mentors are selected on the basis of the observations of research staff. Criteria used to identify candidates are bilingual fluency, engagement in the training, fidelity to the program content, and active listening skills.

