### Intervention design

#### Experimental arm design

The experimental curriculum available in both English and Spanish was developed on the basis of findings from a positive deviance study that identified behaviors and practices from Latino families who were successful in changing their child’s weight status from obese toward a healthy weight [17]. After these behaviors were identified, we used a behavioral intervention mapping approach to create the curriculum for parent mentors to apply with parents in the experimental (positive deviance) arm [22, 23]. The four core behaviors that were identified and developed for this intervention were (1) parent creates a healthy home food environment, (2) parent effectively communicates expectations with other care providers, (3) parent supports small changes to increase children’s outside play time, and (4) parent is consistent about rules related to snacking and food. Intervention mapping attempts to explicitly tie theory and intervention program design through a series of steps that identifies what the behavioral outcomes are and the changes necessary to influence a given outcome [22]. (See Fig. 1 for adapted steps.) In this case, we had identified four core behaviors that we believed were tied to successful weight management in positive deviants; these were our behavioral outcomes (step 2 in Fig. 1).

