#### Intervention frequency (intensity)

Parent–child dyads randomly assigned to the control arm receive health information from the Head Start center their child is enrolled in per the center’s usual care practice. Parent–child dyads randomly assigned to either parent mentor arm attend a 1-hour monthly meeting with their parent mentor and the other mentees in their mentoring group. (See Table 1 for a list of topics and activities.) The parents in the mentoring arms also receive individualized coaching on their goals for that month via weekly phone, text, or in-person follow-up with their parent mentor. The two intervention arms have 4 months of group meetings and individual mentoring followed by 2 months of individual mentoring on a weekly basis. The focus for the weekly communication is to encourage the identified behavior change and problem-solve through any potential obstacles faced.

**Table 1 Tab1:** Topics covered in the two active intervention arms with the parent mentor–led curricula

Month	Positive deviance-based curriculum	*We Can!* curriculum
1	Creating a healthy home food environment	Overview, content, and structure of program. Motivation for eating well and moving more.
2	Effective communication around feeding and physical activity	Introducing the concept of energy balance
3	Supporting outside play time	Managing “energy in” of energy balance
4	Providing consistency, specifically around snacking	Managing “energy out” of energy balance
5	Individual goal setting, support, and troubleshooting (no community meeting)	Individual goal setting, support, and troubleshooting (no community meeting)
6	Individual goal setting, support, and troubleshooting (no community meeting)	Individual goal setting, support, and troubleshooting (no community meeting)

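### The home food environment outcome is parent-reported to the mentors who deliver the curriculum, and its baseline is by inference post-allocation, so the between-curriculum comparison is open to differential reporting bias of unknown size

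*Protocol article*

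**What the plan says.** All references are to the protocol article.

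- **Collector.** Under Secondary outcomes, the home food environment tool is described thus: "This is a parent-reported observation tool". On collection the text continues: "Parent mentors administer the paper survey with parents in their homes and return it to the research office in a stamped envelope".
- **Arms and times.** The same section states: "The home food environment assessment is completed only in intervention and active control dyads at baseline and 4-month follow-up". The other survey measures are taken by interviewer in all three arms at baseline, 6 and 12 months.
- **When a mentor exists for a dyad.** Parent mentor recruitment and training: "Parent mentors are assigned parent mentees after randomization".
- **What the mentor does.** Each mentor is prepared for one curriculum ("The second day of training is specific to the curriculum they are going to use"). Under Intervention frequency (intensity), besides the monthly group meeting, parents receive "individualized coaching on their goals for that month via weekly phone, text, or in-person follow-up with their parent mentor".
- **What is taught.** The first of the four core behaviours in Experimental arm design is "parent creates a healthy home food environment". Month 1 of the positive deviance column in Table 1 is "Creating a healthy home food environment". Month 1 of We Can! is a programme overview and motivation.
- **Use of the result.** Data analysis plans mediation analyses with the secondary outcomes as mediators of the effect on adjusted BMI z-score, and a Holm–Bonferroni adjustment of the secondary outcomes.

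**The concern.** The person who coaches the parent also takes down the parent's answers. That goes beyond the general lack of blinding stated under Randomization, because here the collector is the deliverer of the intervention. If one curriculum tells parents more explicitly than the other what a good answer looks like, reported scores can differ between arms with no difference in the homes.

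A baseline taken after allocation adds to this. It may already carry some effect of the assignment, so neither a change score nor adjustment for that baseline is sure to remove the bias.

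Two results are at stake. One is the comparison of the curricula on a secondary outcome that the Abstract names. The other is the mediation analysis, where a reporting artefact would enter the path from arm to mediator and could be read as the mechanism of the positive deviance content.

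**Working it through.** The plan gives no figure for this outcome. Its only sample size, 64 completers per group, is for BMI z-score, and this point does not depend on it. The main check is to set the passages side by side.

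**1. Is the baseline post-allocation?** The assessment is done only in the two mentor arms, so the arm must be known before the tool is given. It is given by a mentor, and a mentor is linked to a dyad only after randomisation. That it is the dyad's own mentor is the natural reading, though not spelled out; the restriction to two arms leads to the same conclusion without it. The inference is firm for allocation. For the first session it is open: the text is silent, and the schedule in Fig. 3 is not available here.

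**2. Does having mentors in both arms cancel the bias?** It makes the mode, type of collector and timing alike. Content differs:

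| | Positive deviance | We Can! |
|---|---|---|
| Home food environment a named target | Yes: core behaviour and month 1 topic | No |
| Related content by month 4 | Outside play, snacking rules | Managing energy intake and energy expenditure |

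The asymmetry is real but partial. The tool also covers the physical activity environment, which both arms teach.

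**3. Does the reported kappa help?** The threshold of 0.61 concerns agreement between observers on items. It says nothing about what parents tell their own mentor.

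**4. Illustration of size (assumption).** Suppose there is no true difference and a reporting shift of *b* SD between the arms. With *n* per arm, the two-sample t statistic has noncentrality *b*·√(*n*/2) on 2*n* − 2 degrees of freedom. Take *n* = 80 × 0.75 = 60, the enrolment target less the 25% dropout planned by 6 months. Then √30 = 5.477, and *b* = 0.1, 0.2 and 0.3 give 0.548, 1.095 and 1.643.

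The critical values on 118 degrees of freedom are 1.980 at two-sided 0.05 and 2.825 at 0.05/9 = 0.0056. The nine is a count of the domains listed under Secondary outcomes (blood pressure, waist, self-efficacy, feeding practices, diet, physical activity, sleep, screen time, home food environment). The size of the Holm family is therefore also an assumption.

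| Assumed shift | Rejection at first Holm step (nominal 0.56%) | Rejection at unadjusted 5% |
|---|---|---|
| 0.1 SD | 1.3% | 8.4% |
| 0.2 SD | 4.5% | 19.2% |
| 0.3 SD | 12.4% | 37.1% |

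Later Holm steps use looser levels, so the planned procedure lies between the two columns. Retention at 4 months may exceed 60. With all 80 per arm, shifts of 0.2 and 0.3 SD give 6.4% and 18.4% at the first step, and 24.2% and 47.1% unadjusted.

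**The case against.** The strongest reply is that both compared arms use the same mode, collector type and timing, and that by month 4 We Can! has taught about food intake and activity too. The Discussion says that We Can! targets the more traditional diet behaviours and that positive deviance focuses more on parenting skills. The direction of any net shift is therefore uncertain. This stands: the asymmetry is partial, and the documents give neither its size nor its sign. It does not remove the point, because only one curriculum names the measured construct as a target.

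Second, parents are unblinded and taught in either case, so some reporting bias would survive any change of collector. This also stands. The fix reduces the problem and does not abolish it.

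Third, the environment subscale of the Comprehensive Feeding Practices Questionnaire (CFPQ) is taken by interviewer in all three arms at baseline, 6 and 12 months. It is a useful cross-check on a related construct. It does not correct this tool, and it has no 4-month value.

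A reader might infer three stronger things that the documents do not support:

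- *That baseline is taken after mentoring has begun.* No passage says so.
- *That mentor pay gives a motive to inflate scores.* Ethics ties the payment to parents mentored per month, not to answers.
- *That this baseline will be used as a covariate.* Data analysis names only baseline BMI z-score, and secondary outcomes are to be handled by similar methods.

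**Conclusion.** The point holds as a design weakness in one secondary outcome, measured in two arms. Collection by the deliverers of the intervention is explicit, and the post-allocation baseline is a firm inference. The between-curriculum comparison and any mediation analysis that uses the measure are open to differential reporting bias. The primary outcome rests on measured height and weight and is unaffected.

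The size is unknown. The rejection rates above rest on an assumed shift of 0.1 to 0.3 SD that nothing in the documents anchors, on the whole shift being differential reporting, and on a family of nine outcomes. They should not be read as an estimate of the bias in this trial, nor as showing that it favours positive deviance. The Holm–Bonferroni adjustment lowers the false-positive rate but leaves any bias in the estimate untouched.

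The change is worth making because it is cheap and the measure bears closely on the content that separates the two curricula.

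**What to change.** Take mentors out of both administering and handling the tool, obtain the baseline before the assignment is revealed, and use one mode at both time points. Either of two arrangements would do:

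- a research staff interview, at the existing baseline visit and by phone at 4 months; or
- self-completion by the parent at both times, returned directly to the research office in the stamped envelope already supplied.

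If collection cannot change, and for cohorts already collected by mentors (recruitment began in January 2018), classify the measure as an exploratory process measure. Leave it out of the secondary-outcome claims and the mediation analysis, and rely on the interviewer-administered CFPQ environment subscale for this construct. In either case, state when the baseline was taken relative to allocation and to the first session.

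The cost is modest, since forms, envelopes and survey staff exist. The downsides are possibly lower returns, loss of the mentor's help with the check in the home, and a short extra form for control dyads at baseline. Follow-up staff are unblinded too, so the gain is separation from the teacher and not blinded assessment.

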#### Other measures

The stages of change, acculturation scale, and family functioning scales are assessed by interviewer-administered survey at baseline, at the end of the 6-month intervention period, and at the 12-month time point in all three intervention arms. The qualitative interview is completed only with parent mentors.

##### Stages of change

Particularly in preschool-age children, parents underestimate their child’s weight or simply do not think it possible that their child could have obesity or be at an unhealthy weight [38, 39]. Therefore, a stages-of-change questionnaire that has been evaluated as compared with reported parental practice in diet and physical activity domains [40] is administered to parents to better understand how their participation in the trial and any changes in their child’s weight over time may be associated with differences in motivation.

##### Acculturation

The Brief Acculturation Scale for Hispanics (BASH) is administered to parents to assess their degree of acculturation [41]. The BASH has high internal consistency (Cronbach’s alpha = 0.94 overall). This measure assesses language use in different contexts. We added a question specific to dietary acculturation [42]. Parental country of birth and length of time in the US are also collected.

##### Family functioning

Given the targeting of family functioning in the intervention and the role that this may play in feeding practices, we administer the short version (six items) of the General Functioning Scale of the McMaster Family Assessment Device [43]. The short version that asks only about positive aspects of family functioning has been shown to have psychometric properties similar to those of the longer version [44]. The primary respondent, either the mother or father, completes this survey.

##### Qualitative data

We conduct individual, semi-structured interviews with all of the parent mentors at the end of their intervention period. The interviews probe their general experience, perceived effectiveness of the training, challenges and ways they overcame those challenges, and potential ways to modify the program.

### Data analysis

Given the relatively high potential for missing data because of attrition in the population enrolled over time, we plan a procedure of multivariate imputation by chained equations. Variables to be included in the multiple imputation model include BMI z-score of the child, child age, gender, family income, and language. This procedure operates under the assumption that the missing data are missing at random. A pattern mixture model will be applied to examine the informativeness of missing outcome data using time at 6 and 12 months to examine interactions with missing data patterns. The results of the pattern mixture model will be incorporated as a fixed effect in the linear mixed model (described below).

Using an intention-to-treat analysis, we will assess the primary outcome of mean change in adjusted BMI z-score at the end of the active period of intervention and use an alpha of 0.05. We will use linear mixed models to analyze the primary outcome of change in adjusted BMI z-score looking at the main effect of randomization group, time, and their interaction by using Wald tests for statistical significance and Akaike information criterion to assess model fit. A cohort variable, defined as the period of enrollment given multiple enrollment periods over the course of the study, will be included as a fixed effect. Baseline BMI z-score will be examined as a covariate. All models will be examined for the normality, homoscedasticity, and linearity of the residuals to ensure that the assumptions of the models are met.

Secondary outcomes will be analyzed by using similar methods, comparing by randomization group. We will adjust all secondary outcomes for multiple comparisons by using the Holm–Bonferroni method. We will track participation with a potential secondary analysis carried out stratifying by levels of participation. All quantitative analyses will be completed by using SPSS software version 24 (IBM Corporation, Armonk, NY, USA).

We will employ three regression equations to complete planned mediation analyses of intervention effects by the secondary outcomes. These include the main intervention effect on the primary outcome, change in adjusted BMI z-score, the main intervention effect on the mediating variables (secondary outcomes), and the combination of the intervention effect and mediating variables on the primary outcome. We will use a product-of-coefficients approach to examine the potential mediators [45].

Qualitative data will be analyzed by using software from Dedoose (Los Angeles, CA, USA). Coding and identification of emergent themes will be completed by multiple reviewers using a qualitative description approach [46].

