### Sample size

Given the growth patterns of preschool-age children, weight maintenance has been recommended as the goal as this will lead to a reduction in adiposity with expected linear growth [27]. For the power calculations, we used a mean BMI z-score of 2.5 with a standard deviation of 0.7 for the baseline measurements, based on a previous trial in a similar popuation [19]. A BMI z-score of 2.5 is equivalent to a mean of 120% of the 95th percentile BMI for age and gender. Weight maintenance at this age leads to roughly a 0.5-unit reduction in BMI z-score over 4–6 months among children with obesity, a clinically meaningful reduction. We assumed a standard deviation of 1.0 for the 0.5-unit change in BMI z-score over 6 months. With these assumptions and to achieve 80% power at an alpha of 0.05, we would need 64 children per group to complete the 6-month assessment to detect this clinically meaningful difference of 0.5-unit reduction in BMI z-score between the two active intervention groups. We did not include a repeated measures correlation coefficient in our sample size calculation. We estimated a roughly 25% dropout rate by 6 months given the mobility of the targeted population, and so we aimed to recruit and enroll 80 dyads per group (240 parent–child dyads in total).

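### The listed imputation variables include neither randomised arm nor enrolment cohort; if the list is followed as written, the primary contrast is pulled towards zero

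*Protocol article*

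**What the plan says.** All references are to the protocol article.

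- **Data analysis, missing data.** Because attrition may be high, "we plan a procedure of multivariate imputation by chained equations". The variables are then named: "Variables to be included in the multiple imputation model include BMI z-score of the child, child age, gender, family income, and language". On the assumption behind it: "This procedure operates under the assumption that the missing data are missing at random". Nothing in the article says that imputation is done within arm.
- **Data analysis, primary model.** A linear mixed model is fitted, "looking at the main effect of randomization group, time, and their interaction by using Wald tests for statistical significance". Enrolment cohort enters as a fixed effect, baseline BMI z-score is examined as a covariate, and the result of a pattern mixture model is carried in as a further fixed effect.
- **Primary outcome.** "The primary outcome is change in adjusted BMI z-score at the end of the active intervention period, 6 months post-enrollment". The contrast is fixed too: "The primary comparison is between the two active intervention groups at 6 months".
- **Sample size.** The target is a "clinically meaningful difference of 0.5-unit reduction in BMI z-score between the two active intervention groups", with SD 1.0, 80% power and alpha 0.05, which gives 64 completers per group. On attrition: "We estimated a roughly 25% dropout rate by 6 months". Enrolment is set at 80 per group.

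**The concern.** An imputation model should contain at least the terms that the analysis model tests. Here the tested terms are group and group-by-time, and the imputation list has no group variable. A child whose 6-month value is missing would then receive a value drawn from a distribution pooled over all three arms, given age, gender, income, language and BMI z-score. On average such imputed values do not differ between arms. Mixing them with the observed values shrinks the difference between the two mentor arms, and it does so even when data are truly missing at random.

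The contrast affected is the primary one. The Discussion says that, if the two curricula do not differ, having a mentor may itself be sufficient, although it also says that the design cannot establish equivalence. A contrast pulled towards zero would make that reading more likely for a reason unrelated to the curricula. Cohort is a lesser version of the same mismatch: it is in the analysis model but not on the imputation list.

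**Working it through.** **Inputs.** From Sample size: difference δ = 0.5, SD of change 1.0, alpha 0.05 (taken as two-sided), 80 enrolled and 64 completing per group, dropout about 25%, baseline mean 2.5 and SD 0.7. From Randomization: three arms, 1:1:1.

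**1. The plan's own figure.** A two-sample t-test for δ = 0.5, SD 1.0 and 80% power needs 63.8, so 64 per group. The stated figure is reproduced.

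**2. Missing fraction.** Two values can be read from the section. The stated dropout is 25%, which leaves 80 × 0.75 = 60 completers. The targets imply 1 − 64/80 = 20%. Both are carried forward.

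**3. Expected estimate without arm.** Let a fraction d be missing in each mentor arm, and let imputed values have the pooled mean m. The completed-data means are

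- positive deviance: (1 − d) × μ_PD + d × m
- *We Can!*: (1 − d) × μ_WC + d × m

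The term d × m cancels, so the difference is (1 − d) × δ. At d = 0.25 it is 0.75 × 0.5 = 0.375. At d = 0.20 it is 0.80 × 0.5 = 0.40. The usual-care mean drops out.

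**4. Simulation.** 80 per arm, three arms, missingness equal across arms, normal-regression imputation on baseline BMI z-score, 20 imputations, Rubin's rules with small-sample degrees of freedom, t-test on 6-month change, 1,500 trials per setting.

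| Imputation model | Missing | Mean difference | Rejection rate |
|---|---|---|---|
| without arm, δ = 0.5 | 25% | 0.375 | 0.549 |
| with arm, δ = 0.5 | 25% | 0.500 | 0.776 |
| without arm, δ = 0.5 | 20% | 0.402 | 0.646 |
| without arm, δ = 0 | 25% | 0.000 | 0.011 |

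The with-arm power agrees with the t-test on 60 completers per arm (0.775). With 64 completers the t-test gives 0.801.

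**5. Why power falls and the null rate is low.** At d = 0.25 the estimate's true variance is about 0.75² × 2/60 = 0.0188, an SD of 0.137. Rubin's formula reports about 2/80 + 1.05 × (2 × 20/80²) = 0.025 + 0.0066 = 0.0316, an SE of 0.178. The estimate is shrunk and its SE is too large. Under the null the effective threshold is 1.96 × 0.178/0.137 = 2.55 standard deviations, a two-sided rejection rate of about 1.1%, as simulated.

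**6. Recovery from the 12-month visit.** Suppose the 12-month value is used in the imputation, the effect is maintained, and the 6/12-month correlation is 0.8. The last two are assumptions; the article gives neither. With 25% missing at 6 months and arm still left out, the mean estimate is:

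- none of the missing return at 12 months: 0.37
- 30% return: 0.39
- 50% return: 0.44
- all return: 0.48

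These rest on 200 trials each, so they carry a Monte Carlo error of roughly √(2/60)/√200 = 0.013.

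**The case against.** The strongest objection is that the list is not stated to be complete. Its wording says which variables the model includes; it does not say that there are no others. All five are child or family characteristics, which fits a list of covariates added to the analysis variables. The article condenses a fuller protocol, and imputation detail is commonly settled in an analysis plan. This stands as a limit on certainty. A reader might infer that arm will be left out and that the trial will under-report its effect by a quarter; the article does not establish that. The point survives because this is an explicit list, not silence, and an analyst who follows it would build the wrong model.

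A single figure of one quarter is also too firm. It needs 25% loss, equal loss in the two mentor arms, and no help from 12-month data. The enrolment targets imply 20%, and returning children would reduce the dilution. Against that, the Discussion itself expects 12-month contact to be difficult.

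The simulated analysis is a t-test, not the planned mixed model with cohort and a pattern mixture term, so the power figures are approximate. Nothing in the article shows that the pattern mixture step restores an arm difference among imputed children, but its effect was not tested.

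A reader might also infer that the wrong outcome is to be imputed, since the list says BMI z-score without the word adjusted. That is probably shorthand: the Trial status section refers to the primary outcome in the same short way.

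Finally, the error is conservative and cannot manufacture a benefit. That is correct, but it does not make a biased primary estimate acceptable.

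**Conclusion.** The point holds for the list as written. The stated imputation variables contain neither arm nor cohort, while the analysis model in the same section tests group and group-by-time and includes cohort. If the list is followed, the expected primary contrast falls from 0.50 to about 0.375 (power about 55% instead of about 78%) at 25% loss, or to 0.40 (power about 65% instead of about 80%) at 20% loss. If 30% or more of the children missed at 6 months return at 12 months and that value is used, the estimate lies between about 0.39 and 0.48, under the assumed correlation of 0.8 and a maintained effect. Under the null, rejection is about 1–2%.

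These sizes assume equal dropout in the two mentor arms and missingness unrelated to outcome given the imputation variables. Whether arm will in fact be left out cannot be settled from the article. The text should be corrected before the primary analysis because it governs the primary estimate.

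**What to change.** Amend the imputation sentence to state that imputation is done separately by randomised arm, or with arm as a predictor, and that the model includes enrolment cohort and adjusted BMI z-score at baseline, 6 months and 12 months alongside age, gender, income and language. If arm was always intended, the amendment only records it.

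The cost is one line of text, with no extra participants, visits or data. Adding mentor or centre to the imputation model, or making a likelihood-based mixed model on the observed data the primary analysis, would be defensible choices, but neither is needed to correct this point.
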